### Conduct of the study

The study will be divided into two phases: Phase I and Phase II.

#### Phase I

Premenopausal women who are interested to participate will be given brief introduction regarding the trial and offered for blood investigation for serum 25(OH)D, serum calcium, fasting blood insulin, fasting blood glucose, lipid profile and serum PTH as well as anthropometric and blood pressure measurements. Demographic data, sunlight exposure, physical activity and health-related quality of life questionnaires will also be administered at this stage. All the blood samples taken at this stage will be analysed and participants who meet the inclusion criteria will proceed to Phase 2.

#### Phase 2

Selected participants will be randomized into Vitamin D or placebo groups. Informed consent will be obtained from all participants at this stage. The intervention will be given for one year, and participants will be called for blood check at 6 months and 12 months after intervention completes (Figure 
1). Table 
1 shows the outcome measures and time for measurement.

**Figure 1 F1:**
[figure not shown]
Recruitment flow chart.

**Table 1 T1:** Outcome measures and time to be measured

**Measure**	**Months**		
	**0**	**6**	**12**
**Blood analysis**			
Serum 25(OH)D	**x**	**x**	**x**
Serum calcium	**x**	**x**	**x**
Serum PTH	**x**	**x**	**x**
Fasting blood glucose	**x**	**x**	**x**
Fasting blood insulin	**x**	**x**	**x**
Total cholesterol	**x**	**x**	**x**
Triglycerides	**x**	**x**	**x**
HDL-C	**x**	**x**	**x**
LDL-C	**x**	**x**	**x**
**Anthropometry and clinical assessments**			
Height, weight, BMI	**x**	**x**	**x**
Blood pressure	**x**	**x**	**x**
Waist circumference	**x**	**x**	**x**
**Questionnaires**			
Sociodemographics	**x**		
Medical and family history	**x**		
Dietary assessment	**x**		**x**
SF36 version 2	**x**		**x**
Sunlight exposure history	**x**		**x**
IPAQ	**x**		**x**

### Randomization

Eligible participants will be randomized into the active and placebo arm. The randomization sequence will be created using GraphPad Software with a 1:1 allocation by a staff (AC) with no involvement in the trial. The participant’s names will be matched with the random number sequence. The names of participants from intervention and placebo will be printed and pasted on to the tubes filled with either vitamin D powder or placebo. The tubes used will be identical for both active intervention and placebo, and allocation sequence data will be kept by AC in a secure place so that it cannot be accessed or influenced by anyone, including the researchers.

### Vitamin D intervention

The intervention consists of 50,000 IU of cholecalciferol (25(OH)D_3_) supplements with an average weight of 0.5 gram in the form of powder. The vitamin D supplements are purchased from DSM Nutritional products Ltd, Switzerland. Vitamin D supplement will be taken orally by the participants by diluting the powder into warm water before consumption. The consumption frequency will be once a week for 8 weeks (equivalent to 7142 IU/day) and then once a month for maintenance for 10 months (equivalent to 1667 IU/day). The consumption of 50,000 IU of vitamin D per week or per month, is considered to be safe as the tolerable upper intake level for vitamin D is 10,000 IU per day
[37].

The placebo will be identical in taste, texture and colour with the active supplements and will be given the same manner of the active supplement. The vitamin D supplement and placebo will be packed by the Pharmacy Department of the University of Malaya Medical Centre (UMMC). Both the active supplements and placebo will be given to participants in a translucent pill container with only their names on the label. Labelling of the containers will be done by the same person (AC) doing the randomization and allocation sequence. The serum Vitamin D collected at different time points will only be analysed at the end of the trial. This will enable both the researchers and participants to be remained blinded throughout the trial.

To ensure compliance with the intervention, reminders about the intervention appointments will be sent regularly via phone messages, email or phone calls. For those who do not attend the intervention appointment, the researcher will visit them at their workplace to give them the active supplements or placebo personally.

### Blood sampling and methods of analysis

Venous blood samples will be taken by registered staff nurses using a sterile vacutainer needle and needle holder between 7.30 am and 9.30 am. All the participants will be asked to fast overnight for at least 8 hours before blood taking procedure. Blood serum will be used for the analysis of calcium (Ca), PTH, 25(OH)D_3_, fasting blood insulin and lipid profiles. The blood samples will be allowed clotting for about 30 minutes and centrifuged for 10 minutes at 2000 G at 4°C within 2 hours. All the blood serum will be stored at −80°C whilst waiting for analysis. Analysis of fasting blood glucose will be using blood plasma. Homeostasis model assessment of insulin resistance (HOMA-IR) will be used to evaluate insulin resistance. It can be calculated from a simple linear equation based on pairing FBS and Fasting Blood Insulin to establish a measure for insulin resistant: HOMA-IR = FBS (mmol/L) X Fasting Blood Insulin (IU per ml)/22.5. Radioimmunoassay analysis method (DiaSorin, Stillwater, MN) will be used to measure serum 25(OH)D. All tests and analysis will be carried out by the Clinical Diagnostic Laboratory, University Malaya Medical Centre.

### Anthropometry and blood pressure measurement

Blood pressure will be measured twice using a digital sphygmomanometer (OMRON HEM-907 model) in sitting position. The average of two measurements will be taken.

Measurement such as weight and height will be measured using calibrated digital weighing scales (Seca 808, Germany) and stadiometer (Seca, Germany) respectively. Body Mass Index (BMI) will be calculated from the formula of weight (kg)/height^2^(meters). Waist circumference will be measured using circumference measurement tape from the point midway between the iliac crest and costal margin (lower rib) in standing position and after expiration.

### Questionnaires administration

The questionnaires will contain two parts. Part 1 of the questionnaire enquires on socio demographic data, sunlight exposures, physical activity (International Physical Activity Questionnaires – IPAQ) and health-related quality of life questions (SF36® version 2 questionnaires). This questionnaire will be completed by participants at baseline.

The sunlight exposure questions will cover on history of sunlight exposure such as duration of outdoor activity in minutes per day as well as sunlight avoidance history such as usage of umbrella and sun block lotion. Participants are also enquired about their clothing style such as wearing long sleeves and hijab or veil. This questionnaire is obtained from a previous study done at the same setting
[35].

The International Physical Activity Questionnaire (IPAQ) will be used to assess the physical activity patterns. It is a self-administered, 7-day period of IPAQ long form. We are using Malay version of IPAQ (IPAQ-M) and English version of IPAQ for the convenience of our participants in which they can choose to either answer the Malay or English version. IPAQ-M has been validated for use in Malaysian population
[38].

SF-36® version 2 health survey will be used to assess participant’s health-related quality of life on physical and emotional wellbeing for participants with vitamin D deficiency and to assess if any improvements of health-related quality of life after intervention. Permission for usage of this questionnaire will be purchased from QualityMetric’s SF™. This health survey asks 36 questions measuring the functional health and well-being from participant’s point of view. It is a practical, reliable, and valid measure of physical and mental health. The SF-36 version 2 health survey will provide scores for each of the eight health domains, including the physical functioning, role-physical, bodily pain, general health, vitality, social functioning, role emotional and mental health together with psychometrically-based physical component summary (PCS) and mental component summary (MCS). The QualityMetric’s SF™ smart measurement system will be used to automatically calculate the scores. These questionnaires are available in Malay and English version, and it has been validated for use in Malaysian population by Sararaks et al.
[39]. This questionnaire will be administered during screening stage and again at the end of the trial to see if there are any changes in quality of life after the intervention.

Second part of the questionnaire contains a 7-day dietary diary. Participants will be asked to give a detailed description of foods eaten and to estimate the amounts using natural or household measures (e.g. pieces, cups). An experienced dietitian will give instruction on how to fill in the diary. A list of instruction will also be provided in the diary booklet including examples. The dietitian will then convert the estimated amounts using a standardised protocol into weights as well as checking the completeness of the diary prior to data entry into The Nutritionist Pro software. Additional new foods and recipes will be added as required. Vitamin D composition in food will be obtained from The Nutritionist Pro™ Diet Analysis software (Axxya System LLC). After data entry, each record will be verified by a nutrition researcher and corrections will be made if any errors in data entry are found. All volunteers will be given a pre-addressed envelope for the return of the diary to the researcher within 2 weeks upon completion.

### Provision of results to participants

All participants at screening stage will be informed of their anthropometry, blood pressure measurement and blood results. Participants who fail to come to get their results will receive notification of all of their results together with advice about supplementation through mail where applicable.

On completion of the trial, participants will be informed of their current vitamin D status, and if they are taking the active or placebo dose. All participants in the placebo group will be given vitamin D supplements of 50,000 IU per week for 8 weeks and 50,000 IU per month for 4 months upon completion of the trial. Whereas participants taking active dose will be given 50,000 IU per month of vitamin D supplements for 3 months upon completion of the trial.

### Data handling and statistical analysis

We will use Microsoft Access to maintain the demographic data. To record the progress of each participant throughout the trial period, we will use a check box to allow for easy access and follow-up purposes. Raw data obtain from the questionnaire and blood results will be entered into SPSS software version 16.0 (SPSS Inc., 2009, Chicago, Illinois). The data will be cleaned and checked for coding errors. Preferably, data will be double-entered to check for duplication and outliers before commencement of statistical analysis.

For baseline characteristics, descriptive statistics will be used. Categorical data will be described using count, percentages and 95% confidence intervals when applicable. Exact test on proportions will be used to compare categorical variables since this is a comparative trial data. All numerical data will be checked for normality. For normally distributed data, mean with standard deviation, independent t-test will be used and analyse using SPSS 16.0. However, if the data is found to be non-normally distributed or have un-equal variances, exact (permutation) tests will be used. Exact tests analyses will be undertaken using *StatXact*_*®*_ 9 (Cytel Inc.).

The primary analysis will be performed to explore intervention’s effects on HOMA-IR, LDL-cholesterol, TG, HDL and BP These analyses will be following the “intention-to-treat” principle in the comparison between the intervention and the placebo group at 6 months and 12 months. Additionally secondary analyses will be a comparison of change of the vitamin D status and health-related quality of life. Level of statistical significance is preset at p < 0.05.

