**Methods/design:**

Three hundred and twenty premenopausal women working in a public university in Kuala Lumpur, Malaysia will be randomized to receive either vitamin D supplement (50,000 IU weekly for 8 weeks and 50,000 IU monthly for 10 months) or placebo for 12 months. At baseline, all participants are vitamin D deficient (≤ 20 ng/ml or 50 nmol/l). Both participants and researchers will be blinded. The serum vitamin D levels of all participants collected at various time points will only be analysed at the end of the trial. Outcome measures such as 25(OH) D3, HOMA-IR, blood pressure, full lipid profiles will be taken at baseline, 6 months and 12 months. Health related quality of life will be measured at baseline and 12 months. The placebo group will be given delayed treatment for six months after the trial.

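### The only test named for the primary outcomes is an unadjusted two-sample test; the baseline value is not used as a covariate, and follow-up versus change is left unsettled

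*Protocol article*

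**What the plan says.** The methods are in the protocol article under Data handling and statistical analysis. The paragraph that names the tests begins "For baseline characteristics, descriptive statistics will be used" and goes on to numerical data in general: "For normally distributed data, mean with standard deviation, independent t-test will be used and analyse using SPSS 16.0". The fallback is "if the data is found to be non-normally distributed or have un-equal variances, exact (permutation) tests will be used". Both are two-sample tests without covariates.

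The next paragraph sets out the primary analysis: "The primary analysis will be performed to explore intervention’s effects on HOMA-IR, LDL-cholesterol, TG, HDL and BP". It follows intention-to-treat and is a "comparison between the intervention and the placebo group at 6 months and 12 months". No test is named there. The section continues: "Additionally secondary analyses will be a comparison of change of the vitamin D status and health-related quality of life". Change is therefore specified for the secondary outcomes only.

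The Abstract says that outcomes including "full lipid profiles will be taken at baseline, 6 months and 12 months". Table 1 confirms months 0, 6 and 12 for the lipids, for the fasting glucose and insulin behind HOMA-IR, and for blood pressure.

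Under Sample size estimation, the planning figures are a reduction in triglycerides of 0.19 with SD 0.54 mmol/L and a change in LDL-cholesterol of 0.19 with SD 1.03 mmol/L. Both describe change, not level.

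**The concern.** Lipids, blood pressure and HOMA-IR vary far more between women than any plausible treatment effect, and a woman's baseline value predicts part of her later value. An unadjusted test of follow-up values leaves all of that variation in the error term. A test of change scores subtracts the whole baseline value, which over-corrects whenever the correlation is below 1. Regression on the baseline value (ANCOVA) does neither. It also corrects for chance imbalance at baseline, and the data are already being collected.

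The second difficulty is that the analysed quantity is not fixed. If follow-up values are compared, the relevant SD is not the SD of change used for planning, and it is larger whenever the correlation exceeds 0.5. An analyst could defend either choice from this text, and the two give different estimates and different power.

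**Working it through.** **Planning figures first.** For two means, n per arm = 2 × [(1.960 + 0.842) × SD / difference]².

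- Triglycerides: 2 × (2.802 × 0.54 / 0.19)² = 126.8, so 127 per arm; the article states 88.
- LDL-cholesterol: 2 × (2.802 × 1.03 / 0.19)² = 461.3, so 462 per arm; the article states 146.

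Neither stated figure is reproduced. That is a separate sample-size matter, and nothing below depends on it. The differences and SDs are used here only to give the comparison of methods a scale.

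**Inputs.** From Sample size estimation: difference 0.19; SD of change 0.54 (triglycerides) and 1.03 (LDL-cholesterol); two-sided 5%; 160 per arm less 10% attrition = 144 per arm. Assumed, because the article does not give it: the correlation ρ between baseline and follow-up, shown from 0.3 to 0.8. Also assumed: equal SDs at baseline and follow-up, the same SD in both arms, and 0.19 taken as the difference between arms.

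**Formulas.** Let S be the SD of change.

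- SD of follow-up values = S / √[2(1 − ρ)]
- Residual SD under ANCOVA = S × √[(1 + ρ)/2]
- Variance ratio, ANCOVA to follow-up-only = 1 − ρ²
- Variance ratio, ANCOVA to change score = (1 + ρ)/2

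Both ratios are below 1 for every ρ strictly between 0 and 1.

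**Worked case, triglycerides, ρ = 0.6.** The follow-up SD is 0.54/√0.8 = 0.604 and the ANCOVA SD is 0.54 × √0.8 = 0.483. Dividing 0.19 by SD × √(2/144) gives noncentrality 2.67 (follow-up), 2.99 (change) and 3.34 (ANCOVA). The noncentral t distribution then gives power of 76%, 84.5% and 91%.

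**Triglycerides over the range of ρ, 144 per arm:**

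| ρ (assumed) | ANCOVA / follow-up variance | ANCOVA / change variance | Power, follow-up t-test | Power, change t-test | Power, ANCOVA |
|---|---|---|---|---|---|
| 0.3 | 0.91 | 0.65 | 94% | 84.5% | 96% |
| 0.5 | 0.75 | 0.75 | 84.5% | 84.5% | 93% |
| 0.6 | 0.64 | 0.80 | 76% | 84.5% | 91% |
| 0.7 | 0.51 | 0.85 | 63% | 84.5% | 90% |
| 0.8 | 0.36 | 0.90 | 47% | 84.5% | 88% |

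**LDL-cholesterol, ρ = 0.6.** The SDs are 1.152 (follow-up), 1.03 (change) and 0.921 (ANCOVA), and power is about 29%, 34% and 41%.

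ANCOVA has the highest power in every row, so the recommendation depends neither on the unknown ρ nor on which t-test was meant. The size of the gain depends on both.

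**The case against.** The strongest reply is that an unadjusted t-test in a 1:1 randomised trial is valid and unbiased. That stands: this is a point about precision and clarity, not about bias.

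The gain can also be small. At ρ = 0.3 the follow-up test has 94% power for triglycerides against 96% for ANCOVA, and it beats the change-score test. If change was meant, power for triglycerides is 84.5%, already above the 80% target. Both statements are correct, and they are why the whole range is shown.

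The paragraph that names the t-test opens with baseline characteristics, so its use for the primary outcomes is not stated outright. It remains the natural reading, because the paragraph moves on to all numerical data and no other method is given. The abbreviation list includes one-way analysis of variance, but the methods never use it, and it would not adjust for baseline either.

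Two stronger readings are tempting. A reader might infer that the plan ignores baseline altogether. The text does not establish this: the sample size points to change scores, and under that reading baseline is used, only less efficiently. A reader might also infer that the plan analyses only women who attend, against its own intention-to-treat statement. A visit-by-visit test cannot by itself include a woman with no value at that visit. However, the article states no complete-case rule and says nothing about missing outcomes, a detail that a condensed article commonly leaves to the full plan. Silence there is not a contradiction.

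**Conclusion.** The point holds as one of lost precision plus an unsettled analysed quantity. The named tests do not adjust for a baseline value that is available for every primary outcome, and the article does not say whether levels or changes are compared.

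For triglycerides on the article's own inputs, the gain in power from adjustment over the range of ρ is about 2 to 41 percentage points against a follow-up test and about 3 to 11 against a change-score test. For LDL-cholesterol at ρ = 0.6, adjustment raises power to about 41%, which is still far below 80%; it does not repair that shortfall.

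The direction is certain for any ρ between 0 and 1. The size rests on the assumed ρ, on equal SDs at the two visits and in the two arms, and on 0.19 as the difference between arms. The change should be made, but the analysis as written would not be invalid without it.

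**What to change.** In Data handling and statistical analysis, state that each primary outcome will be compared between arms at 6 and at 12 months by a model adjusted for that outcome's baseline value. Two forms would serve:

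- ANCOVA at each visit, with arm and baseline value as terms; or
- one mixed model for both visits, with arm, visit, arm by visit, baseline, and baseline by visit.

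Report the adjusted difference between arms with its 95% confidence interval. Transform skewed outcomes, such as HOMA-IR and triglycerides, where needed. Naming the model also settles follow-up versus change, because with the baseline value as covariate both give the same adjusted arm difference on a common scale.

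The joint model has the further benefit of keeping women seen at only one follow-up visit. It does not recover those with no follow-up value. Which visit is primary is a separate question that this change does not need to decide.

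The cost is wording and a little programming. SPSS, already named, fits both models, and no extra data are needed. The article reports that recruitment was still under way at submission, so the change could have been specified before unblinding.

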Therefore, we proposed to start a RCT with the following objectives:

i. To investigate whether vitamin D supplements can improve cardiometabolic risk factors such as blood pressure (BP), homeostasis model assessment insulin resistant (HOMA-IR), triglycerides (TG) and high-density lipoprotein cholesterol (HDL).

ii. To investigate whether vitamin D supplements can improve the vitamin D status of urban premenopausal women who are vitamin D deficient.

iii. To investigate whether vitamin D supplements can improve the health-related quality of life.

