### Sample size estimation

According to the study by Zittermann et al.
[25], participants from the intervention arm with vitamin D supplementation was found to achieve a reduction in triglycerides of 0.19 ± 0.54 mmol/L and a change in mean for LDL-cholesterol of 0.19+1.03 mmol/L. Sample size calculation was conducted using OpenEpi version 2.3.1 Software. With a power of 80% and a two-sided 5% significant level, a minimum of 88 participants per arm is required using the results on triglycerides, while 146 participants is required with the results on LDL-cholesterol. In order to achieve adequate power, additions of 10% are added to 146 to account for possible attrition. Ultimately, the desired sample size for this study is 160 participants for each arm with a total of 320.

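### Five primary outcomes at two visits share one unadjusted p < 0.05 with no lead outcome or visit, so the chance of at least one false significant primary result is well above 5%

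*Protocol article*

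**What the plan says.** The protocol article, under Data handling and statistical analysis, defines the primary analysis as the intervention's "effects on HOMA-IR, LDL-cholesterol, TG, HDL and BP", by intention to treat, "in the comparison between the intervention and the placebo group at 6 months and 12 months". The same paragraph ranks other outcomes below these: "secondary analyses will be a comparison of change of the vitamin D status and health-related quality of life". It closes with one threshold for everything: "Level of statistical significance is preset at p < 0.05".

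The sample size section uses the same undivided level, "With a power of 80% and a two-sided 5% significant level", for triglycerides and for LDL-cholesterol separately. LDL-cholesterol gives the larger number and so sets the trial size.

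Objective (i) in the Background is to see whether supplements can "improve cardiometabolic risk factors such as blood pressure (BP), homeostasis model assessment insulin resistant (HOMA-IR), triglycerides (TG) and high-density lipoprotein cholesterol (HDL". LDL-cholesterol is not named there. The abstract is broader: "Outcome measures such as 25(OH) D3, HOMA-IR, blood pressure, full lipid profiles will be taken at baseline, 6 months and 12 months".

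The article does not say whether blood pressure is one outcome or two. It states no order of testing and no rule for how many significant results make the trial positive.

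**The concern.** Vitamin D status and quality of life are called secondary, so the five cardiometabolic outcomes were placed in the top tier on purpose. With two visits and one threshold, the article gives 10 or 12 chances for a primary p-value below 0.05 and no way to say in advance which one answers the question. If the supplement does nothing, the chance that at least one of them is significant is several times the nominal 5%.

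This matters because of how the results are meant to be used. The Background notes that earlier trials were inconsistent and asks for conclusive evidence. The Discussion hopes to inform policy on supplementation or fortification. An isolated significant result on one lipid at one visit would be hard to interpret, and nothing in the article limits how it may be presented.

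**Working it through.** **The plan's own figure.** The article states no overall error rate, so there is none to reproduce. The only fixed input is 0.05 per test.

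**Number of tests.** From the statistical analysis section: 5 outcomes × 2 visits = 10. If blood pressure is split into systolic and diastolic (an assumption): 6 × 2 = 12.

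**Upper limit.** For two-sided normal tests, independence gives the largest familywise error, 1 − 0.95^k:
- k = 10: 1 − 0.95^10 = 40.1%
- k = 12: 1 − 0.95^12 = 46.0%

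**With correlation.** The article gives no correlations, so these are assumptions. Multivariate normal test statistics were simulated under no effect (400,000 draws per setting), counting draws with at least one |Z| > 1.96:

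| Correlation between outcomes | Correlation between visits | 5 outcomes | 6 outcomes |
|---|---|---|---|
| 0.2 | 0.5 | 37% | 42% |
| 0.2 | 0.7 | 34% | 39% |
| 0.5 | 0.5 | 31% | 35% |
| 0.5 | 0.7 | 29% | 32% |
| 0.5 | 0.9 | 25% | 28% |

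**Beneficial direction only.** These figures count differences in either direction. Counting only results that favour vitamin D uses 0.025 per test:
- independence: 1 − 0.975^10 = 22.4%; 1 − 0.975^12 = 26.2%
- correlations 0.2–0.5 between outcomes (each signed so that positive means benefit) and 0.5–0.7 between visits: 14.4–19.1% for five outcomes and 16.4–22.0% for six, so roughly 15–22%.

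**12 months alone is not enough.** Under independence, 1 − 0.95^5 = 22.6% and 1 − 0.95^6 = 26.5%. With outcome correlations of 0.2–0.5, simulation gives about 18–22% for five outcomes and 21–25% for six.

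**Cost of Holm, with triglycerides as the example.** Inputs from the sample size section: difference 0.19, SD 0.54 mmol/L. Assume 160 × 0.9 = 144 per arm complete. The noncentrality is (0.19/0.54) × √(144/2) = 2.986.
- At 0.05: 2.986 − 1.960 = 1.026, normal-approximation power 84.7% (t-test 84.5%).
- At the first of six Holm steps, 0.05/6 = 0.0083: 2.986 − 2.638 = 0.348, power about 63.6% (t-test 62.9%).

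The printed 0.19 and 0.54 do not give the article's 88 per arm. The usual two-sample formula gives 2 × (0.54/0.19)² × (1.960 + 0.842)² ≈ 127. The power figures therefore illustrate the cost of Holm. They do not confirm that the trial is adequately powered for triglycerides.

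**The case against.** Several points on the other side have force.

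- **Exploratory wording.** The sentence says the primary analysis is meant to explore effects. That weakens the case for a strict confirmatory standard but does not remove it: the same sentence calls the analysis primary, the trial is sized on formal tests, and policy use is foreseen.
- **No success rule.** A reader might infer that any one significant result makes the trial positive. The article does not say so, nor does it require all outcomes or a pattern. The 29–42% depends on that reading.
- **Direction.** A reader might take these figures as the chance of a false claim of benefit. They are not, because they include results against vitamin D. The beneficial direction alone is about half.
- **Upper end.** About 45% needs near-independence of 12 tests. That is implausible for systolic with diastolic pressure or for the same lipid six months apart, and the split of blood pressure is itself not in the text.
- **LDL-cholesterol.** A reader might see a contradiction between objective (i) and the primary analysis. The objective introduces its list as examples, and the abstract refers to full lipid profiles, so this is only untidy.
- **A separate analysis plan.** An adjustment may exist in a document not shown, so its absence can be stated only of this article. That does not remove the point: the article itself fixes the primary set, both visits and the undivided 0.05.

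**Conclusion.** The concern holds in limited form. As written, the article has five primary outcomes (six if blood pressure is split) at two visits, each at 0.05, with no lead outcome or visit. If none is affected and one significant result is enough, the chance of at least one is at most 40% or 46%, about 29–42% under moderate assumed correlation, and about 25–28% under very strong correlation. Even the lowest figure is about five times the nominal 5%.

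The stronger conclusion, that an ineffective supplement has a 30–45% chance of being declared beneficial, is not supported. It adds a decision rule the article does not state and counts harmful as well as beneficial differences. Nor do the documents support calling triglycerides the one outcome that 160 per arm powers: its printed inputs do not reproduce the stated 88, and no inputs are given for HOMA-IR, HDL or blood pressure.

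**What to change.** Before unblinding, make 12 months the only primary time point and 6 months secondary. The Trial status section says recruitment is still under way, so this is a change of wording. Then choose one of two routes:

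1. The sponsor names one primary outcome and makes the others secondary. That outcome keeps the full 0.05 and loses no power. The price is that the others can no longer carry the primary conclusion.
2. Keep the set and apply Holm across it at 12 months, stating whether blood pressure counts as one outcome (and which measure) or two. Familywise error is then held at 5%, but power per outcome falls. In the triglyceride example it drops from about 84% to about 63% at the first of six steps.

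As tidying, treat LDL-cholesterol the same way in objective (i), the sample size paragraph and the primary analysis.
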